## Abstract

Implicit and explicit motor learning processes work interactively in everyday life to promote the creation of highly automatized motor behaviors. The cerebellum is crucial for motor sequence learning and adaptation, as it contributes to the error correction and to sensorimotor integration of on-going actions. A non-invasive cerebellar stimulation has been demonstrated to modulate implicit motor learning and adaptation. The present study aimed to explore the potential role of cerebellar theta burst stimulation (TBS) in modulating explicit motor learning and adaptation, in healthy subjects. Cerebellar TBS will be applied immediately before the learning phase of a computerized task based on a modified Serial Reaction Time Task (SRTT) paradigm. Here, we present a study protocol aimed at evaluating the behavioral effects of continuous (cTBS), intermittent TBS (iTBS), or sham Theta Burst Stimulation (TBS) on four different conditions: learning, adaptation, delayed recall and re-adaptation of SRTT. We are confident to find modulation of SRTT performance induced by cerebellar TBS, in particular, processing acceleration and reduction of error in all the conditions induced by cerebellar iTBS, as already known for implicit processes. On the other hand, we expect that cerebellar cTBS could induce opposite effects. Results from this protocol are supposed to advance the knowledge about the role of non-invasive cerebellar modulation in neurorehabilitation, providing clinicians with useful data for further exploiting this technique in different clinical conditions.

## Introduction

Motor learning can be defined as the set of processes, which allow creating internal abstract models of motor behavior. Each internal abstract model refers to a set of input-output relations between the generated (planned) motor commands and the subsequent environmental and internal consequences (1). These models entail two main components: the first one is defined by the spatial/sequential order in which movement modules are assembled into a defined action, the other one subserves action adaptation with respect to the individual and environmental needs (2–4). Learning how to ride a bicycle exemplifies the entire process, which entails different motor sequences to organize into a specific action schema: putting hands on handlebars, sitting on the saddle, positioning the feet on the pedals, applying muscle strength alternatingly on both legs, and propelling forward. These repetitive, modular motor sequences do not necessarily guarantee a good action outcome because of continuous adjustments, which depend on both the internal and external factors that need to be constantly adopted to fine-tune “on-going” actions (2, 4).

The motor learning process allows acquiring internal actions models through “allocentric” frames, and favors continuous adaptation to the specific needs and environmental circumstances using “egocentric” frames (5–7). Abstracted, goal-based, allocentric motor schemata are finally stored in the cortical-subcortical networks and enable the automatic performance of complex actions (8). Motor adaptation properly modulates these internal models of action based on egocentric, contextual, environmental, and ever-changing conditions for improving the action performance over time (4). In this context, one could think of how differently a bicycle ride might be by an inexpert amateur in comparison with a professional biker.

The internal models of motor behavior result from both implicit and explicit processes of learning (3, 9).

Differences between these two learning modalities do not account for the resulting internal abstract model, but refer to the generating process itself, which could be volitional and attention-demanding or conversely, unconscious, and non-attention based (9–11). The dissociation between procedural and declarative memory concerns the internal model and the distinctions between their verbally expressible and verbally inexpressible aspects (9, 12).

Motor learning results from activity in a complex cortico-subcortical network, which entails different areas, such as the motor cortex, the prefrontal cortex, the parietal cortex, the basal ganglia, and the cerebellum (1, 4, 13). Although the imaging data have so far not provided definitive evidence of a specific role of each area in the different phases of learning, consistent results indicate a crucial role of the cerebellum for motor sequence learning and motor adaptation, as it subserves error correction of on-going actions and contributes to sensorimotor integration (13–15).

Knowledge about motor learning has relevant, practical, and applicative values in neurorehabilitation, as principles of motor learning can be applied to the methodologies designed to promote clinical recovery in neurologically affected patients (16–18). The non-invasive brain stimulation techniques (NIBS), eventually combined with standard physical therapy (19–23), were shown to be effective in fostering and maximizing motor learning resources (24–29).

Augmentation of motor learning through the application of NIBS has previously been attempted in implicit motor learning paradigms (30–32). Indeed, modulation of the cerebellum was considered effective and easy, given the role this area plays in motor learning (33, 34).

The effect of a non-invasive cerebellar stimulation has been tested in various motor tasks (30, 35–44). A cerebellar repetitive transcranial magnetic stimulation (rTMS) induces long-lasting changes in the excitability of the contralateral primary motor cortex (M1) (45, 46) and may interfere with the cerebellar cognitive functions (47). Excitatory and inhibitory rTMS can also be administered in the form of TBS with the same efficacy and safety, but with the great advantage of requiring much shorter application times and lower stimulation intensities (48).

Recently, Koch et al. (49) demonstrated acceleration of motor adaptation following excitatory intermittent TBS (iTBS), applied to the right cerebellar hemisphere. Furthermore, TMS combined with electroencephalogram (TMS-EEG) revealed relevant changes of cortical activity in the interconnected motor networks induced by cerebellar iTBS (49). Block and Celnik (50) previously demonstrated enhancement of motor learning after anodal transcranial direct current stimulation (tDCS) of the right cerebellum but no effect in inter-manual transfer.

To date, the literature lacks studies exploring the explicit acquisition of allocentric motor sequences and the explicit, ego-centered adaptation of execution of the same sequences using different effectors (e.g., inter-manual transfer conditions). This is certainly a prominent aspect, considering the value and the effectiveness of explicit strategies in the field of neurorehabilitation.

To address explicit motor sequence learning, the Serial Reaction Time Task (SRTT) (5, 51, 52) was specifically designed (53). The participants are asked to perform a choice reaction time task, which consists of visual stimuli that appear on a screen in a fixed and repetitive sequence, and which requires moving specific parts of the body (usually fingers). It follows that the learning of a motor sequence will be implicitly or explicitly induced. Two variables, the reaction times and the accuracy of responses, permit analyzing both components of the learning process: acquisition of the movement sequence (the allocentric frame) and its adaptation (the ego-centric frame).

A study aimed to investigate the effects of cerebellar iTBS, continuous (cTBS), or sham TBS, in modulating both explicit motor sequential learning and motor adaptation in healthy subjects is presented.

## Materials and Methods

### Population

In this randomized, double blind experimental study, 40 healthy, right-handed participants were enrolled. Hemispheric dominance was assessed through the Edinburgh Handedness Inventory (EHI) (54). The inclusion criteria followed in the study were: (i) age 18–80 years, (ii) absence of visual or auditory disturbances possibly impacting on neuropsychological evaluation, (iii) no previous medical-neurological conditions considered as exclusion criteria for TMS (55), and (iv) no previous psychiatric diseases.

### Study Design

The participants will be divided into four groups—age, sex, and educational-matched. All the participants will undergo two experimental sessions on a single-day, separated by a break of 45 min, each one including two behavioral tasks based on a modified SRTT paradigm (51–53). Before each session, patients will be subjected to one specific type of cerebellar TBS (Figure 1).

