#### Behavioral Tasks

Serial Reaction Time Task was programmed using SuperLab 5 (Cedrus, San Pedro, CA, USA) and will be administered in a laboratory setting, with constant artificial light and without auditory interference. The hand to be used for the learning task will be randomized, and the contralateral hand subsequently will perform the adaptation task. The participants will seat on a chair in front of a computer screen, where four aligned blue squares will be presented simultaneously. As soon as one of these squares turns red (visual cue), participants are supposed to press as fast as possible the corresponding one of four aligned buttons on a keyboard with the corresponding index, middle, ring, or little finger (D2, D3, D4, and D5, respectively) of the selected hand. Immediately after correct key selection, the visual cue disappeared and the trial ends. After an interval of 200 ms, a new visual cue appeared and a new trial begins. Twelve consecutive trials correspond to the sequence that participants had to learn explicitly. The sequence needs to follow a specific set of rules: (a) the same visual cue does not appear two times successively; (b) each visual cue appears three times; and (c) visual cues are pseudo-randomized. The sequence to be learned is: 2–4–1–3–2–4–3–1–2–4–1–3. The same sequence will be used in each of the four experimental conditions: (1) Motor sequence learning (MSL), in which participants learn the sequence; (2) Adaptation (AD), in which participants are required to execute the learned sequence with the opposite hand; (3) Delayed recall (DR), in which the participants are required to recall the adapted sequence execution after a 45-min break; (4) Re-adaptation (RA), in which the participants have to return back to execute the sequence with the hand that originally learned the sequence (as shown in Figure 1). In MSL, participants will be required to learn the 12-item sequence presented in a 13-consecutive series, each series repeated four times with an inter-series-interval of 1 min. The same procedure will be repeated after 5 min. In AD, participants performed the same 13-consecutive series of 12-item sequences four times, with an inter-series-interval of 1 min with the opposite hand. In DR, participants repeated the AD task after 45 min and following another stimulation protocol (according to group assignment). Finally, in RA, participants will perform the 12-item sequence with the “original” hand in 13-consecutive series, will repeat four times with an inter-series-interval of 1 min. Errors, i.e., wrong key strokes, were counted (accuracy). The time taken to select the correct key will be recorded (response time, RT) (Figure 2).

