### Statistical Analysis

#### Behavioral Task Analysis

Shapiro–Wilk's statistic supported by visual inspection will be used to test the normality of distribution of all variables. Descriptive statistics of collected data will be reported as mean ± SD for continuous variables and as percentage frequencies for categorical variables. To assess data distribution, the variables will be examined by the Kolmogorov-Smirnov (K-S) test. One-way ANOVA will be used to compare differences in baseline values among groups. The effects of two independent variables (groups: specifically, G1 vs. G2; G3 vs. G4; G1 vs. G3; G2 vs. G4; task; MSL, DA, DR, and RA), on both accuracy and RTs of motor skill learning will be evaluated using two-way repeated measures ANOVA.

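### Groups are matched on age, sex and education, but the two-way ANOVA contains only group and task, so between-group tests are conservative if those factors predict the outcome

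*Protocol article*

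**What the plan says.** - **Population:** "In this randomized, double blind experimental study, 40 healthy, right-handed participants were enrolled". The eligible age range is "age 18–80 years".
- **Study Design:** "The participants will be divided into four groups—age, sex, and educational-matched". The section does not say how the matching works together with the randomisation.
- **Theta Burst Stimulation:** G1 and G2 receive iTBS and sham in opposite orders. G3 and G4 receive cTBS and sham in opposite orders.
- **Behavioral Task Analysis:** the model is introduced with "The effects of two independent variables (groups: specifically, G1 vs. G2; G3 vs. G4; G1 vs. G3; G2 vs. G4; task", followed by the four conditions, and is a two-way repeated measures ANOVA for both accuracy and response time. It lists no term for age, sex, education or matched set.
- **Behavioral Task Analysis, baseline data:** "One-way ANOVA will be used to compare differences in baseline values among groups". This compares the groups and adjusts nothing.

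**The concern.** When groups are balanced by design on a factor that predicts the outcome, the difference between group means varies less from one realisation to the next than it would under unrestricted allocation. An ANOVA without that factor does not register the gain. The spread due to the factor remains in the between-person error term, so the reported standard error exceeds the true one. The test then rejects less often than its nominal level, and power is lost.

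This matters here for two reasons. First, one outcome is a response time measured in people aged anywhere from 18 to 80, so age may account for a material share of the between-person variance. Second, some central comparisons are between different people. Stimulation precedes the first task and the article describes no task run before it, so active versus sham at motor sequence learning (MSL) compares one group with another. With about 10 people per group there is little precision to spare.

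**Working it through.** The article gives no SD, effect size, alpha or power for this comparison, so there is no planned figure to reproduce.

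**Inputs from the article:** 40 participants; four groups; pairwise group contrasts; four tasks; model factors group and task; matching on age, sex and education.

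**Assumptions:** equal split, 40/4 = 10 per group; two-sided alpha 0.05; R², the share of between-person outcome variance explained by the matching factors, from 0 to 0.5. A pairwise contrast has 10 + 10 − 2 = 18 error df.

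**Step 1, upper bound by formula.** If matching were perfect, reported SE / true SE = 1/√(1 − R²). This gives 1.054, 1.195 and 1.414 at R² = 0.1, 0.3 and 0.5. At R² = 0.5 the actual size is about 2 × P(t on 18 df > 2.101 × 1.414) = 0.008.

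**Step 2, imperfect matching by simulation.** In 40,000 runs per setting, 20 people were paired on one prognostic score, assigned at random within pairs, and analysed on one outcome value per person, with and without the score. SEs are in SD units; power is at a true difference d of 1 SD.

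| R² | True SE, unadjusted difference | Mean reported SE, unadjusted | Mean reported SE, adjusted | Type I error, unadjusted | Type I error, adjusted | Power, unadjusted | Power, adjusted |
|---|---|---|---|---|---|---|---|
| 0 | 0.447 | 0.441 | 0.441 | 0.049 | 0.049 | 0.562 | 0.556 |
| 0.1 | 0.426 | 0.442 | 0.418 | 0.039 | 0.050 | 0.565 | 0.604 |
| 0.3 | 0.381 | 0.445 | 0.369 | 0.021 | 0.050 | 0.564 | 0.712 |
| 0.5 | 0.325 | 0.447 | 0.312 | 0.009 | 0.049 | 0.568 | 0.847 |

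The simulated SE ratios, 0.442/0.426 = 1.04, 0.445/0.381 = 1.17 and 0.447/0.325 = 1.38, lie just below the bounds in step 1, as they should.

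**Step 3, cost of three covariates.** The simulation spends one df on the score. With three covariates the error df are 18 − 3 = 15. Noncentral t power at d = 1 is then 0.597, 0.705 and 0.840 at R² = 0.1, 0.3 and 0.5. At R² = 0 it is 0.552, against 0.562 unadjusted in the table, a loss of about 0.01.

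**Step 4, which terms are affected.** The full two-way repeated measures ANOVA was simulated (10,000 runs, four tasks, intraclass correlation 0.7 assumed, covariate effect constant over tasks):

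| R² | Type I error, group main effect | Type I error, group × task |
|---|---|---|
| 0.3 | 0.025 | 0.050 |
| 0.5 | 0.012 | 0.053 |

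A covariate effect that is the same at every task cancels within a person, so the interaction keeps its nominal size.

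**Step 5, if matching achieves nothing beyond simple random allocation.** The unadjusted test keeps its size (0.050 to 0.052 for R² from 0.1 to 0.5). Adjustment still narrows the mean SE, from 0.441 to 0.430, from 0.440 to 0.379 and from 0.441 to 0.321.

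**The case against.** **The error is in the safe direction.** An unadjusted test after matching does not inflate type I error; it only costs power. That is correct and limits the seriousness of the point.

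**The key term may be untouched.** In G1 vs G2 and G3 vs G4 both groups receive the same two stimulations in opposite order, so the group main effect averages over active and sham, and the interaction carries much of the stimulation effect. In G1 vs G3 and G2 vs G4 both groups receive sham in one session, which dilutes the main effect. This stands, and it confines the problem to the main effect and single-task contrasts. It does not remove the problem: the authors expect iTBS to help in all phases, all four tasks use the same sequence, and a learning benefit that persists from session 1 would appear in the main effect.

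**Covariates may be in an analysis plan not shown.** That is possible, and the article does not expressly exclude them. But it states both the matching factors and the model factors, and the two do not agree.

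**The size rests on assumptions.** R² is not in the article. The simulation pairs closely on a single score; balancing three factors at once would be looser, so the true size would lie between the figures shown and 5%. No separate figure is available for accuracy.

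**Stronger readings.** A reader might infer from the wording on dividing and matching that assignment was by judgement and open to selection bias. The article does not support this. Its Population section calls the study randomised, and stratified randomisation, minimisation and randomisation within matched sets all produce matched groups. A condensed article may leave the mechanism to the full protocol. The separate statement "The hand to be used for the learning task will be randomized" adds a second randomised element; it does not imply that the stimulation group was not randomised. A reader might also infer that sex is to be tested by ANOVA. The article says only that baseline values are compared, and that categorical variables are reported as percentages.

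**Conclusion.** The point holds in a limited form. The design restricts allocation on three named factors and the stated model omits them. Where those factors predict the outcome, tests of the group main effect and of group differences at a single task are conservative. At R² of 0.1 the loss is small; at 0.3 to 0.5 a 5% test runs at roughly 2% to 1%, and adjustment would recover about 15 to 28 percentage points of power at d = 1 (0.712 − 0.564 and 0.847 − 0.568). For scale, 10 versus 10 unadjusted reaches 80% power only at d of about 1.32. These figures assume equal groups, two-sided 5% alpha and close matching. The group × task interaction is not affected unless the factors also change the differences between tasks.

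On allocation, what remains is a lack of clarity between two sections. It is not evidence of non-random assignment. The two matters also differ in kind: wide standard errors cost power, whereas assignment by judgement would risk bias that adjusting for three factors would not fully remove.

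**What to change.** 1. In Behavioral Task Analysis, prespecify age (continuous), sex and education as covariates in the response time and accuracy models. Entered as one df each, they use about 3 of 18 error df per pairwise contrast. If formal matched sets were used, a set term is an alternative, but ten sets would take 9 of the 18 df in a pairwise contrast.
2. If age is thought to change the differences between tasks, say in advance whether an age-by-task term is included, since only then would the interaction test also be affected.
3. Do not rely on the baseline one-way ANOVA to deal with the matching factors. A descriptive table by group is enough.
4. Make Population and Study Design agree, in one sentence, on how matching is combined with random assignment to stimulation group. If assignment was not random, the design label needs correcting.

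None of this needs new data or more participants. The article describes enrolment in the past tense, but the model and the wording can still be settled before analysis. If the factors turn out not to predict the outcome, the price is about 0.01 of power at d = 1.

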**Figure 1 F1:**
[figure not shown]
Study design. See the text.

#### Theta Burst Stimulation

Group 1 (G1) will receive cerebellar iTBS before the session 1 and sham stimulation before the session 2; group 2 (G2) will receive cerebellar sham stimulation before the session 1 and cerebellar iTBS before the session 2; group 3 (G3) will receive cerebellar cTBS before the session 1 and sham stimulation before the session 2; group 4 (G4) will receive cerebellar sham stimulation before the session 1 and cerebellar cTBS before the session 2 (as shown in Figure 1).

Theta burst stimulation protocols will be carried out using a Magstim Super Rapid stimulator (Magstim Company, Whitland, UK) and a 70 mm figure-of-eight coil. TBS stimulation intensity will be set at 80% of the active motor threshold (AMT), defined as the lowest intensity which evoked at least five out of 10 MEPs with an amplitude > 200 μV peak-to-peak amplitude in the first dorsal interosseous (FDI) muscle during 10% of maximum voluntary contraction (56). This stimulation intensity was previously shown to produce plastic changes in the contralateral primary motor cortex (M1) (57). The iTBS protocol consists of a 2 s train of TBS repeated 20 times, every 10 s for a total of 190 s (48). The cTBS protocol consists of three-pulse bursts at 50 Hz repeated every 200 ms for 40 s (48). TBS will be applied over the lateral cerebellum, i.e., 1 cm inferior and 3 cm lateral to the inion (57). A cerebellar TBS is expected to modulate neural activity in the interconnected contralateral motor and parietal areas (57, 58). The coil will be positioned tangentially to the scalp, with the handle pointing superiorly; for sham TBS, it will be angled away so that no current was induced in the brain (59). Sham TBS will be delivered with an intermittent pattern in G1 and G2 and with continuous pattern in G3 and G4.

#### Behavioral Tasks

Serial Reaction Time Task was programmed using SuperLab 5 (Cedrus, San Pedro, CA, USA) and will be administered in a laboratory setting, with constant artificial light and without auditory interference. The hand to be used for the learning task will be randomized, and the contralateral hand subsequently will perform the adaptation task. The participants will seat on a chair in front of a computer screen, where four aligned blue squares will be presented simultaneously. As soon as one of these squares turns red (visual cue), participants are supposed to press as fast as possible the corresponding one of four aligned buttons on a keyboard with the corresponding index, middle, ring, or little finger (D2, D3, D4, and D5, respectively) of the selected hand. Immediately after correct key selection, the visual cue disappeared and the trial ends. After an interval of 200 ms, a new visual cue appeared and a new trial begins. Twelve consecutive trials correspond to the sequence that participants had to learn explicitly. The sequence needs to follow a specific set of rules: (a) the same visual cue does not appear two times successively; (b) each visual cue appears three times; and (c) visual cues are pseudo-randomized. The sequence to be learned is: 2–4–1–3–2–4–3–1–2–4–1–3. The same sequence will be used in each of the four experimental conditions: (1) Motor sequence learning (MSL), in which participants learn the sequence; (2) Adaptation (AD), in which participants are required to execute the learned sequence with the opposite hand; (3) Delayed recall (DR), in which the participants are required to recall the adapted sequence execution after a 45-min break; (4) Re-adaptation (RA), in which the participants have to return back to execute the sequence with the hand that originally learned the sequence (as shown in Figure 1). In MSL, participants will be required to learn the 12-item sequence presented in a 13-consecutive series, each series repeated four times with an inter-series-interval of 1 min. The same procedure will be repeated after 5 min. In AD, participants performed the same 13-consecutive series of 12-item sequences four times, with an inter-series-interval of 1 min with the opposite hand. In DR, participants repeated the AD task after 45 min and following another stimulation protocol (according to group assignment). Finally, in RA, participants will perform the 12-item sequence with the “original” hand in 13-consecutive series, will repeat four times with an inter-series-interval of 1 min. Errors, i.e., wrong key strokes, were counted (accuracy). The time taken to select the correct key will be recorded (response time, RT) (Figure 2).

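### The trial randomises the learning hand, but the ANOVA holds only group and task, so any hand difference goes into the within-subject error that tests Group x Task

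*Protocol article*

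**What the plan says.** **Hand.** Under Behavioral Tasks: "The hand to be used for the learning task will be randomized, and the contralateral hand subsequently will perform the adaptation task". In adaptation (AD), "participants are required to execute the learned sequence with the opposite hand". Delayed recall (DR) repeats the AD task, and re-adaptation (RA) returns to the hand used in motor sequence learning (MSL). Each participant thus uses one hand in MSL and RA and the other in AD and DR.

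**Participants.** Under Population, "40 healthy, right-handed participants were enrolled". Under Study Design, "The participants will be divided into four groups", matched on age, sex and education. Learning hand is not a matching factor.

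**Stimulation.** Under Theta Burst Stimulation: "TBS will be applied over the lateral cerebellum, i.e., 1 cm inferior and 3 cm lateral to the inion". The text names neither left nor right and does not link the site to the learning hand. The same section gives the mechanism: "A cerebellar TBS is expected to modulate neural activity in the interconnected contralateral motor and parietal areas". The Introduction describes earlier iTBS work "applied to the right cerebellar hemisphere", but the Methods text does not say that this study uses that side.

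**Model.** Behavioral Task Analysis fixes a two-way repeated measures ANOVA for accuracy and response time. It refers to "The effects of two independent variables" and lists them as group, in four pairwise comparisons, and task.

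**The concern.** A factor that the trial itself randomises is missing from a model whose factors are named and counted. In right-handed people the two hands may well differ in speed and accuracy. Because the hand changes between tasks, such a difference raises some of a participant's task scores and lowers others, and the direction depends on the learning hand. A model without hand treats this pattern as noise, in exactly the error term that tests Group x Task. That interaction carries the study question, because active and sham stimulation swap between sessions in G1 v G2 and in G3 v G4.

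A second issue is conditional. The stated mechanism is contralateral, so the effect may depend on which hand performs relative to the stimulated side. The two-factor model cannot show this, whichever rule sets the side.

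**Working it through.** **No figure to reproduce.** The article states no alpha, power, effect size or SD. Everything below is an illustration. It assumes 40/4 = 10 per group, learning hand allocated 1:1, two-sided alpha 0.05, and variance 0.5 between plus 0.5 within participants (SD 1 within a task). The hand difference is h SD.

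**1. Where the hand difference goes.** Each participant uses each hand in two of the four tasks, once per session. The hand contribution to the participant's mean is the same for everyone, so it cancels there. In simulation (4,000 runs, 10 v 10, 5/5 hands per group) the between-participant mean square stayed near 2.5 for every h.

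Within participants, each task score departs from its group-by-task mean by +h/2 or -h/2. The sum of squares per participant is 4 x (h/2)^2 = h^2. Over 20 participants, on (20 - 2) x 3 = 54 error df, the within-subject error mean square is 0.5 + 20h^2/54:
- h = 0.5: 0.5 + 0.093 = 0.593 (simulated 0.595)
- h = 1.0: 0.5 + 0.370 = 0.870 (simulated 0.871)

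Standard errors based on this pooled term grow by sqrt(0.593/0.5) = 1.09 and sqrt(0.870/0.5) = 1.32.

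**2. Single-task contrasts.** The SD within a task becomes sqrt(1 + h^2/4), which is 1.03, 1.12 and 1.25 for h = 0.5, 1.0 and 1.5. For a true effect of 1.32 SD, two-sample t power falls from 0.80 to 0.77, 0.70 and 0.61.

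**3. Fixed side: dilution.** If only one hand responds and hands split 1:1, the mean effect in each task is 0.5 x d + 0.5 x 0 = d/2. If the other hand responds half as much, it is 0.5d + 0.5(d/2) = 0.75d. Two-sample t power, 10 v 10:

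| True effect d | No lateralisation | Partial (0.75d) | Full (0.5d) |
|---|---|---|---|
| 0.8 | 0.40 | 0.25 | 0.13 |
| 1.0 | 0.56 | 0.36 | 0.18 |
| 1.32 | 0.80 | 0.55 | 0.29 |
| 1.5 | 0.89 | 0.66 | 0.36 |

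**4. Both parts together.** Simulated Group x Task power for a 0.8 SD effect of active stimulation:

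| h | Both hands respond: without hand / with | One hand responds: without hand / with |
|---|---|---|
| 0 | 0.99 / 0.99 | 0.39 / 0.51 |
| 0.5 | 0.98 / 0.99 | 0.20 / 0.49 |
| 1.0 | 0.93 / 0.99 | 0.04 / 0.50 |

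In the one-hand case, the error mean square without hand is 0.62, 0.86 and 1.29. The model 'with hand' here crossed hand with both group and task, leaving (20 - 4) x 3 = 48 error df and an error mean square of about 0.50. The smaller addition of learning hand and learning hand x task leaves 54 - 3 = 51 error df and removes the whole h part. It leaves a group-specific remainder of +/-0.2 in each of four tasks, or 0.16 per participant, so the error mean square is 0.5 + 20 x 0.16/51 = 0.56.

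The value 0.04 is extreme. A 5/5 split removes hand from the group-by-task means but not from the error, which makes the test conservative.

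**5. Side follows the learning hand.** MSL and RA are then always performed with the hand on the stimulated side, and AD and DR never. No task mixes the two, so there is no dilution within a task. Laterality is instead a relabelling of MSL/RA v AD/DR.

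**6. Chance imbalance.** Under simple randomisation, two groups of 10 differ by at least 3 right-hand starters with probability 0.26, and by at least 4 with probability 0.12. With h = 0.5, a difference of 3 shifts a single-task contrast by (3/10) x 0.5 = 0.15 SD.

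**The case against.** **Missing detail.** The figures are not shown and the article condenses a fuller protocol, so the stimulated side and the method of randomising the hand may be given elsewhere. This stands: the unnamed side alone is not a finding. It does not rescue the model, which the article states with exactly two factors.

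**Bias.** A reader might infer that unequal numbers of left-hand and right-hand starters bias the group contrasts. The design does not support this. Hand is randomised, so contrasts are unbiased in expectation, and a pure hand effect, including any chance imbalance, cancels from participant means. Only Group x Task and single-task contrasts are exposed, and the harm there is lost precision and chance imbalance in the realised sample.

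**Dilution.** A reader might also infer that the effect is certainly halved. That needs a fixed side and a fully hand-specific effect, and the article states neither. It treats sequence acquisition as allocentric, so full hand-specificity in MSL is not its premise. The power losses in the dilution table come from single-task t-tests and are not the power of the planned ANOVA.

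**Averaging may be intended.** Inter-manual transfer is part of the question, and randomising the hand avoids tying task to dominance. Each session uses both hands after one stimulation, so a one-hand effect would be halved at session level even with a fixed learning hand. This is fair as a defence of the randomisation. It gives no reason to leave the randomised factor out of the analysis.

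**Conclusion.** The point holds as a loss of precision that can be avoided at little cost. Under the stated variance assumptions, a hand difference of 0.5 to 1.0 SD raises the within-subject error mean square by about 19% to 74% (0.593/0.5 and 0.870/0.5). If both hands respond to stimulation, the effect on power can be small: 0.98 v 0.99, or 0.93 v 0.99, in the simulated case. The loss becomes large only if the effect is also lateralised and the side is fixed. Dilution is then the main cost: even with hand in the model, simulated power is about 0.5, against 0.99 when both hands respond.

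Which laterality problem applies depends on the side rule: dilution of up to half with a fixed side, or confounding with task if the side follows the learning hand. In the second case active v sham comparisons within a task remain valid, and only the interpretation of differences between tasks is limited. All power values rest on assumed effects, SDs, equal groups and 1:1 hand allocation.

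**What to change.** 1. Add learning hand and learning hand x task to the planned model for accuracy and response time. In each pairwise group comparison this costs 1 between-participant df (18 to 17) and 3 within-participant df (54 to 51).
2. State the stimulation side rule in force and how it relates to the learning hand.
3. If the side is fixed, report as secondary a mixed model with a stimulation x performing-hand laterality term (same side as the stimulation, or opposite). Laterality changes from task to task, so the two-way ANOVA as written cannot carry it. With about 5 participants per group-by-hand cell, treat the result as exploratory.
4. If the side follows the learning hand, state that laterality and task cannot be separated, and limit claims about learning v adaptation accordingly.
5. Where allocation is not yet complete, block learning hand within group (5/5). The Population section describes enrolment in the past tense, so this may be too late. Items 1 to 4 remain available before analysis and need only changes of wording and code.

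Adding learning hand recovers precision. It does not undo dilution, which is why item 3 is needed as well.
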